### Blinding

The surgery team will not be blinded because the small incisions made during the surgery will be different in each case. Patients will also not be blinded, as the incisions will be visible during postoperative wound care. To reduce the bias associated with data collection, the outcome assessor will be separate from the surgery team and blinded to the allocation.

### Perioperative management

Patients in both groups receive treatment for colon cancer using the same strategy, according to the National Comprehensive Cancer Network Guidelines. Perioperative management is standardised at all institutions [7]. One day before surgery, all the patients will be completing the mechanical bowel preparation, except for those with right-sided colon cancer, for whom the preparation will be selectively administered according to the surgeon’s discretion. On the day of surgery, prophylactic broad-spectrum antibiotics will be administered before the incision. Surgery will be performed using a laparoscopic approach, for which one 11-mm camera port is placed at the periumbilical area and three or four 5-mm trocars are used. A modified complete mesocolic excision with central vascular ligation will be performed according to the location of the tumour [8]. A small incision for specimen extraction will be made according to group allocation. Stapled anastomosis will be performed extracorporeally through a small incision, except for cases of anterior resection, for which intracorporeal colorectal anastomosis is performed.

### Intervention

A small incision will be made by extending the periumbilical port for the camera scope in both groups. The size of the small incision will be determined based on the size of the tumour and the physical habits of the patient. The fascial closure methods are standardised as continuous closure using Stratafix (SF Symmetric PDS Plus®) with a 4:1 ratio (4-to-1 suture to wound length ratio) and bites of < 1 cm. The methods for closure of the subcutaneous fat and skin (skin stapler or 3–0 nylon vertical mattress) depend on the surgeon’s discretion. Patients randomly assigned to the midline group will undergo an incision along the midline skin, subcutaneous fat, and linea alba.

In the non-muscle-cutting periumbilical transverse group, the method of small incision is the same as in a previous report (Fig. 2) [6]. Briefly, the skin incision of the 11-mm periumbilical port will be extended transversely. Using monopolar electrocautery and crossing linea alba, the anterior and posterior rectus sheaths are transversely incised. With lateral traction of the rectus abdominis muscle with an army retractor, the posterior rectus sheath can be seen (Supplemental Video 1). The transversalis fascia and parietal peritoneum are further incised transversely. Continuous fascia closure will be separately performed for the anterior and posterior rectus sheaths. Implementing vertical or transverse incisions will not require alteration to usual care pathways (including the use of any medication), and these will continue for both trial arms.

**Fig. 2 Fig2:**
[figure not shown]
**A** Transverse skin incision. **B** Transverse incision of the anterior fascia of the rectus abdominis muscle. **C** Transverse incision of the posterior fascia of the rectus abdominis muscle. **D** Incision completed. Note. This figure was produced by [name] in 2022. From **“**Periumbilical Transverse Incision for Reducing Incisional Hernia in Laparoscopic Colon Cancer Surgery,” by [name] et al., 2022, World Journal of Surgery,46(4): p918. Copyright 2022 by SPRINGER

### Outcomes (schedule of outcome measurement)

Data will be collected at the baseline (before surgery), during the hospital stay, at 30 days, and at 6, 12, and 36 months after surgery (Table 1). The primary outcome of this study is the incidence of incisional hernias, including both symptomatic and radiologic hernias, at 12 months after surgery. Incisional hernia is assessed by interviewing patients regarding subjective symptoms, performing a physical examination of the abdomen, and reviewing abdominal-pelvic computed tomography (CT) scans. An incisional hernia is defined as either a symptomatic hernia during the interview or a radiologic hernia when it is diagnosed on both an abdominal-pelvic CT scan and a physical examination in cases where subjective symptoms do not exist. The secondary outcomes are the length of hospital stay, estimated blood loss, pain numerical rating scale (0: no; 10: worst pain imaginable) score on postoperative days 1, 2, and 3; reoperation, open conversion, 30-day postoperative complications, (as classified by the Clavien–Dindo classification) [9], surgical site infection (as classified by the Center for Disease Control and Prevention criteria [10] and ASEPSIS score [11]), 30-day mortality, the incidence of repair of incisional hernias, pathologic result of colon cancer (pathologic stage, histologic type, differentiation, number of harvested and metastatic regional lymph nodes, lymphovascular, venous, and perineural invasion, and distant metastasis), and patient-reported outcomes (short form-12 health survey questionnaire before surgery, and at 12 months after surgery and Body Image Questionnaire at 12 months after surgery) [12, 13]. The incidence of incisional hernia at 36 months after surgery is another secondary outcome that will be separately analysed and reported after the last patient enrolled completes the follow-up.

**Table 1 Tab1:** Schedule for assessment, interventions, and follow-up

Time point (visit number)	Baseline V0	Operation V1	1 month V2	6 months V3	12 months V4	36 months V5
Assessment						
Eligibility assessment						
Consent	X					
Demographics						
Baseline data	X					
Colonoscopy	*					
Operative outcomes		X				
30-day morbidity		X	X			
30-day mortality		X	X			
Symptomatic hernia			X	X	X	X
Radiologic hernia				X	X	X
Pathologic report			*			
Adjuvant chemotherapy				*		
Body image questionnaire					X	
SF-12	X				X	

Assessments undertaken as routine care for colon cancer are displayed with an asterisk

*SF-12*, short form-12 health survey questionnaire

### Withdrawal of patients

The participants are free to discontinue their participation at any time for any reason without any consequences. If a participant meets newly established or previously unrecognised exclusion criteria or has an urgent medical condition that disqualifies them from participating, the investigator may opt to remove them from the research. Patients who withdraw their consent after randomisation but before surgery will be replaced, whereas those who withdraw their consent after surgery will not be replaced. The data from these patients will not be included in the analysis.

### Data management and control

Participants’ identities will be kept private by using a research identification number that cannot be linked to their identities. Each centre will keep all patient-identifiable information in the file, apart from the data needed for analysis. To ensure consistent assessment, researchers will be uniformly trained. The result assessor at each centre will first input data into a registered paper-based case report form before entering it into the predesigned electronic version of the case report form. Both the paper and electronic versions of the case report forms will be maintained in a safe location, with only the members of the research team having access to them. All records will be stored for inspection at any time during and for 3 years after the completion of the study report. The study will be monitored by a committee of the Chonnam National University Hwasun Hospital.

Day-to-day support will be provided by the principal investigator (like supervision of the trial, recruitment, and medical responsibility of the patients) and the research coordinator (including data collection and follow-up of the patients) of each participating institution. The principal investigator and research coordinator will meet weekly. The Trial Steering Committee (TSC) will consist of representatives from participating institutions, which will act as a decision-making committee and be responsible for the scientific conduct of the study. The TSC will meet every 3 months, ensure that the trial is conducted following relevant principles, and provide overall supervision.

#### Frequency and procedures for auditing trial conduct

The Institutional Review Board (IRB) of each participating institution will continue to review the trial. The TSC will check the consent forms, compliance with the protocol, planned surgical interventions, and quality of data collected in the case report forms at least annually.

#### Composition of the data monitoring committee, its role, and its reporting structure

The Data Safety and Monitoring Board is independent of the sponsor, has not worked with the study team, and does not have competing interests. The Data Safety and Monitoring Board will meet every 6 months to review the study procedures and adverse events (AEs). Each AE is to be classified by the investigator according to the Common Terminology Criteria, version 5.0 [14]. Serious AEs and AEs of special interest are captured and processed until the last visit of the last patient. A final list will be provided to the ethics committee. All serious AEs will be additionally graded according to the Clavien-Dindo classification of postoperative complications.

#### Plans to promote participant retention and complete follow‑up

During follow-up, several strategies, such as collecting detailed contact preferences and sending text messages in advance, will be used to maximise participant retention. Up to five contact attempts will be made before participants are considered lost to follow-up.

### Sample size estimation

This study aimed to test the superiority of the non-muscle-cutting periumbilical transverse incision over the midline incision, and the sample size was estimated based on the primary outcome (the incidence of incisional hernia at 12 months after surgery). Our previous retrospective study showed that the incidence of incisional hernias was 2.4% and 14.9% in non-muscle-cutting periumbilical transverse and midline incisions, respectively [6]. For this study, a conservative estimate rounded these incidences up to 2.5% and 15%, respectively. The sample size calculations were conducted in R using the pwr (pwr.2p.test); the required sample size for a superiority trial was determined to be 158 patients using power analysis (power = 85%, *ɑ* = 0.05, two-sided), and the dropout rate was anticipated at 10%. Finally, a total of 176 patients are required for randomisation.

### Statistical analysis

Data analysis will be performed using primary analysis (ITT), followed by secondary analysis (as-treated principles). The ITT set includes all patients who were randomised regardless of whether they received each incision, and the “per-protocol” analysis set includes patients who were treated according to protocol, excluding major protocol violations. Given our expectation, very few patients will crossover between incision types. All baseline and outcome data will be presented using frequencies with proportions for categorical variables and means with standard deviations for continuous data (or medians with interquartile ranges, whichever is more appropriate). The patients will be compared based on their baseline characteristics, including age, sex, body mass index, American Society of Anaesthesiologists classification, preoperative treatment (none, radiotherapy, or chemotherapy), comorbidities, medications, history of previous abdominal surgery, location of the tumour (right or left), and baseline short form-12 health survey questionnaire to determine the balance between the two groups. The primary outcome (the incidence of incisional hernia) will be analysed using the chi-square test. The secondary outcomes will be analysed using the chi-square test for categorical variables (i.e. type of surgery, resection, and anastomosis, incidence of 30-day postoperative complications, histologic type, and depth of the tumour), and Student’s *t*-test or Mann–Whitney *U* test for quantitative variables (i.e. operative time, length of hospital stay, blood loss, postoperative pain scores, size of the tumour, and the number of lymph nodes) as appropriate. In accordance with symptoms, each incision type will be evaluated during follow-up after surgery. However, it is not expected that there will be missing data relating to the primary outcomes. For other possible missing data, multiple imputations will be made, based on the assumption that the data are missing at random.

Subgroup analyses will be conducted for each randomisation stratum. The results will be evaluated at a significance threshold of *p* < 0.05 (two-sided). All of the statistical analyses will be performed using *R* statistical software, version 3.4.3 (R Foundation for Statistical Computing).

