### Randomisation

Participant screening will be done by the surgeon and confirmed by the research coordinator of each institution. If potential participants meet all protocol eligibility protocol and agree to the informed consent forms, the investigators will enrol the participants and call the research coordinator of the initiating institution (Chonnam National University Hwasun Hospital) the day before the surgery and inform them of which group the registered patient is assigned to. In-hospital patients will be preoperatively allocated in a 1:1 ratio to either the midline or non-muscle-cutting periumbilical transverse incision groups, after stratifying by the location of the tumour (right-sided: caecum-transverse colon; left-sided: descending-rectosigmoid colon), according to the random sequence generated by a web-based randomisation system. The randomisation sequence will be generated independently by the designated staff not involved in outcome data collection and analysis before being provided to the randomisation contract for onward use. A unique study identification number will be assigned to the patients during data collection and analysis to ensure anonymityThe allocation information will also be blinded to the data analyst, and it will remain blinded to the public until a final comparison is performed.

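### Minor: the primary chi-square test leaves out the tumour-side stratum used in randomisation, and judging each side separately at p < 0.05 would give discordant results about half the time under a uniform effect

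*Protocol article*

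**What the plan says.** All references are to the protocol article.

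- **Randomisation:** patients are allocated 1:1, "after stratifying by the location of the tumour (right-sided: caecum-transverse colon; left-sided: descending-rectosigmoid colon").
- **Statistical analysis, primary outcome:** "The primary outcome (the incidence of incisional hernia) will be analysed using the chi-square test". Tumour location appears elsewhere in that section only in the list of baseline characteristics compared for balance.
- **Statistical analysis, subgroups:** "Subgroup analyses will be conducted for each randomisation stratum". The next sentence begins "The results will be evaluated at a significance threshold of" and sets two-sided p < 0.05, without separating the primary result from the subgroup results.
- **Sample size estimation:** the assumed 12-month risks are 2.5% (transverse) and 15% (midline). At 85% power and two-sided α = 0.05 they give 158 patients, raised to 176 for 10% dropout.

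**The concern.** Two stated choices fit the design poorly.

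First, a factor used to stratify randomisation would normally be carried into the primary analysis. Here it is not.

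Second, the factor is used for two separate within-side comparisons, and the only criterion stated for any result is p < 0.05. Each side holds about half of a trial sized for one overall comparison, so each side is underpowered. One significant and one non-significant side is then an ordinary outcome even if the incision works equally well on both. A reader could conclude that the transverse incision helps on one side of the colon only. That matters because the Discussion presents the periumbilical site as suitable for extraction from any part of the colon.

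**Working it through.** **Inputs from the document.** Risks 15% and 2.5%; two-sided α = 0.05; power 85%; 158 patients, so 79 per arm; two strata.

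**Inputs assumed.** The right/left split and any difference in risk between sides are not given. The base case is 40 and 39 per arm with the same risks on both sides. Other values are shown as ranges.

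**1. The plan's own figure.** With the arcsine effect size:
- h = 2·asin(√0.15) − 2·asin(√0.025) = 0.478
- n per arm = 2 × ((1.960 + 1.036)/0.478)² ≈ 78.6, rounded up to 79, so 158 in total
- 158/0.90 = 175.6, rounded up to 176

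Both stated numbers reproduce.

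**2. Does leaving out the stratum harm the primary test?** Power at 79 per arm, by exact enumeration for the equal-risk chi-square and simulation for the rest. Where side is prognostic, the risk ratio is held constant:

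| Midline risk, side A / side B | Unstratified chi-square | CMH, uncorrected |
|---|---|---|
| 15% / 15% | 85.2% | 83.6% |
| 20% / 10% | 85.5% | 84.4% |
| 25% / 5% | 86.1% | 86.3% |

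The difference (CMH minus chi-square) runs from −1.6 to +0.2 points. Over five null settings, type I error is 4.6–5.3% for the unstratified test and 4.7–5.0% for CMH. Neither is a concern.

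**3. Within-side tests under one common effect (15% v 2.5%).** Let u and v be the exact power on each side. Then P(exactly one significant) = u(1 − v) + v(1 − u).
- Uncorrected, 40/39 per arm: u = 0.577, v = 0.565. Exactly one: 0.577 × 0.435 + 0.565 × 0.423 = 0.49. Both: 0.577 × 0.565 = 0.33. Neither: 0.423 × 0.435 = 0.18.
- Continuity-corrected, 40/39 per arm: u = 0.311, v = 0.297. Exactly one: 0.311 × 0.703 + 0.297 × 0.689 = 0.42. Both: 0.09. Neither: 0.48.
- Other splits, from 44/44 (no dropout) to 24/55 per arm: exactly one 47–57% uncorrected, 42–52% corrected.
- Same risk ratio with side prognostic, 40/39 per arm, uncorrected: exactly one 56% (midline risk 20%/10%) and 75% (25%/5%).

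**4. Within-side tests under no effect.** Two independent tests at 0.05 have a nominal chance of 1 − 0.95² = 9.75% of at least one significant side. Exact values at a common risk of 8.75% are 9–12% uncorrected and 2–3% corrected.

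**5. Sparse strata.** The expected hernia count per arm in a stratum of 40 is 40 × 0.0875 = 3.5 at the average risk. In the transverse arm it is 40 × 0.025 = 1.0, and the chance of no hernia there is 0.975⁴⁰ = 0.36. This affects how an interaction test should be specified.

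**6. Continuity correction.** At 79 per arm, the corrected unstratified chi-square has exact power of 73.5% and type I error of about 2.1%, against 85.2% and 5.3% uncorrected. With all 88 per arm evaluable, power is 79.6% and 87.9%.

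**The case against.** The strongest reply is that nothing in the primary result is wrong. A reader might infer that an unstratified test after stratified randomisation is invalid, or that the strata are tested in place of the overall comparison. The documents support neither. The pooled intention-to-treat test remains the primary analysis, the strata are additional, and step 2 shows error and power essentially unchanged. CMH falls slightly below the planned 85% when side is not prognostic. This part of the objection stands, and it keeps the point minor.

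A reader might also infer that a false one-sided claim is likely. That goes too far. The 49% is the chance of discordant p-values under a real common effect and an assumed equal split. A claim would also need someone to misread that pattern, and the article does not say that a subgroup p-value will support a conclusion. If there is no effect at all, a significant side is uncommon (step 4).

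Third, the plan names R but neither a function nor a continuity correction, so the roughly 73% power is not a property of the plan as written. It is only a reason to state the variant.

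Finally, an interaction test and an exploratory label may sit in an analysis plan that is not shown, and their absence alone is no finding. What remains rests on stated text: a primary test with no stratification, and per-stratum analyses covered by a general p < 0.05.

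**Conclusion.** The point holds as a minor, inexpensive improvement. The primary test does not use the randomisation factor, but the numerical consequence is small: type I error about 5%, and power within 2 points of CMH.

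The more useful part concerns the strata. With the plan's own effect on both sides and an equal split, judging each side at p < 0.05 gives exactly one significant side 49% of the time uncorrected and 42% corrected. Across the assumed splits the range is 42–57%. Such a pattern would therefore say almost nothing about whether the effect differs by side.

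These figures rest on the 15% and 2.5% risks, 79 evaluable patients per arm unless stated otherwise, and an assumed right/left split. They do not show that the primary analysis is invalid or underpowered as written.

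**What to change.** 1. **Primary test:** CMH stratified by tumour side, stated to be without continuity correction, with the Mantel-Haenszel risk difference and 95% CI.
2. **Strata:** one treatment-by-side interaction test. Fix its scale in advance and choose a form that tolerates zero cells, such as the risk-difference scale or an exact homogeneity test, since a transverse stratum may have no hernias. A non-significant interaction should not be read as proof that the sides are alike.
3. **Reporting:** give stratum risk differences with exact or score CIs, labelled exploratory, with no significance claim for either side. Limit the p < 0.05 sentence accordingly.

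**Cost:** one paragraph of wording, no new data and no change in sample size. If side is not prognostic, power falls by up to about 1.6 points (83.6% v 85.2%). If side is strongly prognostic, the loss disappears.

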**Methods:**

This is an open-label, multi-centre, parallel, superiority, and randomised trial. Altogether, 174 patients will be allocated in a 1:1 ratio to either the midline incision or the non-muscle-cutting periumbilical transverse incision group, after stratifying by the location of the tumour (right- or left-sided). The primary outcome of this study is the incidence of incisional hernias (both symptomatic and radiologic hernias) at 12 months after surgery. The secondary outcomes include operative outcomes, 30-day postoperative complications, pathological results, and patient-reported outcomes (short form-12 health survey questionnaire and body image questionnaire). Both primary (intention-to-treat) and secondary (as-treated principles) analyses will be performed for all outcomes. The statistical significance level was set at *p* < 0.05 (two-sided testing).

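### SF-12 is collected before surgery and at 12 months, but the only analysis stated for quantitative secondary outcomes makes no adjustment for baseline, which costs precision

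*Protocol article*

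**What the plan says.** The abstract lists among the secondary outcomes the "patient-reported outcomes (short form-12 health survey questionnaire and body image questionnaire". The Outcomes section gives the timing: "short form-12 health survey questionnaire before surgery, and at 12 months after surgery and Body Image Questionnaire at 12 months after surgery". Table 1 agrees, marking SF-12 at the baseline visit (V0) and the 12-month visit (V4), and the body image questionnaire at V4 only.

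The Statistical analysis section gives one rule for secondary outcomes: a chi-square test for categorical variables, and Student's t-test or a Mann–Whitney U "test for quantitative variables (i.e. operative time, length of hospital stay, blood loss, postoperative pain scores", followed by tumour size and number of lymph nodes. It names no covariate, regression model or change-score analysis. Baseline SF-12 appears in that section once, at the end of the list of baseline characteristics to be compared: "baseline short form-12 health survey questionnaire to determine the balance between the two groups".

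**The concern.** When an outcome is measured before and after treatment, the baseline value usually explains part of the variation in the later score. A two-sample test on the later score leaves that part in the error term, so the confidence interval is wider than it needs to be. Comparing baseline scores between the groups does not recover this precision, and the article states no step that follows from the comparison.

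The sample size was set for hernia incidence, so nothing in the design secures a given precision for SF-12. It is the only patient-reported outcome listed with both a baseline and a follow-up value, and patients already supply the baseline. At stake is the precision of one secondary outcome.

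**Working it through.** **1. Inputs from the document.** Sample size estimation assumes 2.5% and 15% hernia incidence ("a conservative estimate rounded these incidences up to 2.5% and 15%, respectively"). The required number was "determined to be 158 patients using power analysis (power = 85%, *ɑ* = 0.05, two-sided", and "the dropout rate was anticipated at 10"%. Allocation is 1:1. The article gives no SF-12 standard deviation, target difference or correlation.

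**2. The plan's own figure.** With the arcsine effect size, h = 2·asin(√0.15) − 2·asin(√0.025) = 0.478. Then n per arm = 2·((1.960 + 1.036)/h)² = 78.6, so 79 per arm and 158 in total. Allowing for dropout, 158/0.90 = 175.6, so 176. The stated numbers reproduce. They concern the primary outcome and serve here only to supply 79 per arm.

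**3. Variance factors.** Let r be the correlation between baseline and 12-month SF-12, with equal variances at both times and the variance of a t-test on the 12-month score set to 1.

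- ANCOVA: 1 − r²
- t-test on change scores: 2(1 − r)
- ANCOVA relative to change scores: (1 − r²)/[2(1 − r)] = (1 + r)/2, a reduction of (1 − r)/2

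**4. Power for a fixed difference.** With 79 per arm and two-sided 0.05, a t-test on the 12-month score has 80% power for a difference of (1.960 + 0.842)·√(2/79) = 0.446 SD. Power of the other analyses for that same difference is Φ(2.802/√v − 1.960), where v is the variance factor.

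| Assumed r | ANCOVA variance factor | Reduction vs 12-month score | CI width ratio vs 12-month score | Equivalent total N (158/factor) | Reduction vs change score | Power, 12-month score | Power, change score | Power, ANCOVA |
|---|---|---|---|---|---|---|---|---|
| 0.3 | 0.91 | 9% | 0.95 | 174 | 35% | 80% | 65.8% | 83.6% |
| 0.5 | 0.75 | 25% | 0.87 | 211 | 25% | 80% | 80.0% | 89.9% |
| 0.7 | 0.51 | 49% | 0.71 | 310 | 15% | 80% | 95.1% | 97.5% |

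ANCOVA is the most precise of the three in every row. These figures use the normal approximation, ignore the negligible cost of estimating the baseline slope, and credit no gain to tumour side. They apply to the t-test; the comparison with a Mann–Whitney test would depend on the shape of the score distribution.

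**The case against.** **SF-12 is not named in the list.** The bracketed variables are perioperative and pathological, and no sentence assigns a test to SF-12. This stands as a limit: coverage is an inference. The inference is reasonable, because the sentence is about the secondary outcomes in general. Its lists also leave out others such as the body image score, reoperation, 30-day mortality and surgical site infection, so they read as examples.

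**The article condenses a fuller protocol, so the model could be settled elsewhere.** This would answer a complaint of silence. But the article does state a rule for secondary outcomes, and that rule is unadjusted.

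**The t-test might be applied to change from baseline, which does use the baseline.** The wording allows this, so a reader who infers that the plan discards the baseline altogether goes further than the text. The size of the gain depends on which score is tested, which is why both comparators are shown. ANCOVA is at least as precise as either.

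**The correlation is assumed.** This stands. Baseline precedes cancer surgery and follow-up is a year later, so a low value is plausible. At r = 0.3 the interval narrows by only about 5% relative to a test on the 12-month score.

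**No error is shown.** This also stands. A reader might infer that chance baseline imbalance biases the unadjusted comparison. Under randomisation it does not: the estimate is unbiased over repeated allocation, and its standard error already reflects such imbalance.

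**Conclusion.** The point holds as a free gain in precision for one secondary outcome. The article states only unadjusted two-group tests for quantitative secondary outcomes, while a baseline that would sharpen the SF-12 comparison is already collected. For r between 0.3 and 0.7, ANCOVA cuts the variance by 9% to 49% relative to a test on the 12-month score, and by 35% to 15% relative to a test on change scores; at r = 0.5 both reductions are 25%. This rests on the inference that the general rule covers SF-12, on the assumed range of r, and on about 79 patients per arm providing both SF-12 scores.

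Two stronger readings should be avoided. Quality of life is not shown to be a main argument for the new incision: the Background mentions it as something hernias impair, while the stated hypothesis concerns hernia incidence and cosmesis. Nor does the point reach the primary analysis or the sample size, which reproduces as stated.

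**What to change.** Add to the Statistical analysis section that the 12-month SF-12 physical and mental summary scores will each be compared by a linear model with arm, baseline score and tumour side (the randomisation stratum) as terms, reporting the adjusted mean difference with its 95% confidence interval. Keep the unadjusted tests for quantitative outcomes without a baseline value, such as the body image questionnaire, length of stay and blood loss.

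The cost is one or two sentences, settled before the comparison by arm is run. No extra visits, questionnaires or patients are needed.
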